## Abstract

**Background/Introduction:**

Though considered a late-onset disease, the 2020 report of the Lancet Commission emphasizes the necessity of conducting primary prevention trials with an approach of never too early in the life course for dementia prevention. Driven by the same notion, we hereby aim to compare the dementia risk reduction potential of two potential interventions, 48 weeks (12 months) of yoga and brisk walking, in middle-aged high-risk subjects.

**Design:**

A randomized controlled trial.

**Setting:**

Community in India.

**Participants:**

In total, 323 at-risk dementia subjects will be recruited from community settings through health awareness camps and door-to-door surveys across Delhi, India. Participants will be randomized into yoga or brisk-walking groups (1:1). The yoga intervention group will receive 60 contact yoga sessions per 60-min/day at the community parks, followed by continued tele-supervised home practice, further followed by at-home self-practice, and will be tested at 3-time points (baseline, 24-week and 48-week, post-randomization) to test the efficacy of the intervention. The control group will be asked to do brisk walking daily for 45 minutes at their convenience, followed by weekly telephone follow-ups. Applying the intention-to-treat principle, the primary endpoint will be the change from baseline at the 12th month in the Cardiovascular Risk Factors, Aging, and Dementia (CAIDE) Scores. Secondary outcomes will include the composite scores derived from a comprehensive neuropsychology battery, comprising the Trail Making Test, Digit Span Test, N Back, Color Trail, Animal Fluency Test, COWA (Controlled Oral Word Association Test), and Digit Symbol Substitution. The primary outcome will be analyzed using mixed-effect models for repeated measures, adjusted for covariates as fixed effects. The study has been prospectively registered (CTRI/2023/02/049746) on February 15, 2023. The protocol was conceptualized in 2021 and approved by the Institutional Ethics Committee of SVYASA. Recruitment began in February 2023 and is underway with patient enrollment.

**Conclusion:**

To our knowledge, this is the first controlled trial to investigate the longitudinal effects of a yoga-based intervention on dementia risk reduction using the CAIDE risk score. The findings of this trial will also provide insight into a better understanding of genotype-dependent responses to yoga intervention and open up avenues for understanding the implications of gene-intervention interactions for precision prevention using yoga.

## Introduction

**T**he global trends of population aging have tremendously impacted life expectancy in the Southern Asian region (1). India, the most populous country in the world, is at an alarming stage of population aging, with an estimated share of 20% of individuals aged 60 years or older by 2050 (2). Increased dementia is one of the primary consequences of population ageing. The latest estimates by the Longitudinal Aging Study in India (LASI) indicate a 7.4% prevalence of dementia, with 8.8 million individuals being afflicted (3). Dementia refers to a diverse range of conditions, with Alzheimer’s disease and vascular dementia being the most prevalent types (4). Unfortunately, there are no effective therapies available yet to treat dementia. Positively, the pathological model of dementia provides an optimal window for its prevention given the lengthy course of its duration, which takes several years to emerge (5). Hence, early and accurate identification of people at high risk of dementia is critical for the effective implementation of preventive measures. The importance of modifiable risk factors highlights the risk of dementia (5). Detecting changes in these risk factors before the disease manifests clinically allows for timely and careful management of vascular risk factors, thereby delaying the onset of the disease (5). The Lancet Commission on Dementia Prevention, Intervention, and Care Report states that up to one-third of dementia cases are preventable, considering the key potentially reversible risk factors.

Non-pharmacological physical activity-based therapies have shown potential for reducing the risk of dementia (6, 7). The prevention model for dementia is based on the estimation of risk reduction using the Cardiovascular Risk Factors, Ageing, and Dementia (CAIDE) score. This score was developed to address the increasing need for early detection in the treatment of neurodegenerative diseases. The CAIDE score is a validated tool for estimating dementia risk derived from age, sex, education, systolic blood pressure, body mass index, serum total cholesterol, and physical activity in middle-aged community subjects and has been validated to estimate the risk of dementia 20 years later (10). However, the reported associations between physical activity and dementia risk reduction have not been established using the intervention. Mechanistically, exercise and physical activity-based interventions have been proposed to possibly work via attenuating the vascular risk and associated vascular cognitive impairments, thereby halting the advancement of neurodegenerative diseases and dementias. Yoga has a mechanistic basis that can effectively manage cardiovascular risk factors (8). We deemed that testing the same over a composite score like the Cardiovascular Risk Factors, Ageing, and Dementia (CAIDE) score would aid in the translation of the existing evidence to support the preventive potential of yoga for dementia. We also hypothesize a concomitant improvement in cognitive functions.

The causes of dementia are varied, but genetic variations in the apolipoprotein E (ApoE) gene have been identified as major factors contributing to the disease. This conclusion comes from extensive genome-wide association studies (GWASs) (11), which have been confirmed by studies in different populations worldwide, including Asian Indians (12, 13). ApoE plays a key role in both cerebral and peripheral cholesterol metabolism and underlies many functions involved in brain amyloid metabolism, blood-brain barrier integrity, and transport of various lipid species to neuronal cells, as well as in hepatic uptake of triglyceride-rich lipoproteins (13). Interestingly, the genotype of ApoE has also been reported to play an important role in response to interventions (14). ApoE is a significant genetic component that has been validated across many cohorts around the globe, including the Indian population (15). Exercise has been reported to be more beneficial in ApoE4 carriers than non-carriers towards amyloid deposition (16). To our knowledge, no study has explored the risk reduction associated with adherence to yoga and its plausible modification by ApoE ε4 allele status.

### Study Design

The study DERRY (Dementia Risk Reduction using yoga will be a prospective, parallel-group, single-center, and 2-arm randomized controlled trial wherein the subjects will be randomly allocated to two groups: yoga or active walking control. The protocol has been drafted following the CONSORT guidelines (Consolidated Standards of Reporting Trials) (17) (Figure 1). The study will be conducted between February 2023 and October 2024. A total of 323 adults (aged 30-65 years) with dementia risk (CAIDE score≥6) will be recruited from the community set up through door-to-door surveys and dementia awareness camps across Delhi, India. Eligible participants will be randomized into 1:1 yoga or active control groups. Primary and secondary outcomes will be assessed at baseline (before intervention) and at 24 and 48-week visits (with a 60-day window of flexibility) (see Figure 1). All participants will follow their usual medical regime during the study period. This protocol (RES/IEC-SVYASA/243/2022) has been approved by the Ethics Committee of Swami Vivekananda Yoga Anusandhana Samsthana. Interested and eligible individuals will be asked to attend an orientation session, and informed consent will be obtained from them before participation.

**Figure 1 F1:**
[figure not shown]
Participant flow chart for parallel design, based on the Consolidated Standards of Reporting Trials guidelines for transparent reporting of trials. CAIDE: cardiovascular risk factor, aging, and incidence of dementia

## Recruitment and screening

Participants will be enrolled using convenience sampling between February 2023 and October 2024. Middle-aged individuals, aged 39 to 65 years, will be eligible if they have not regularly practiced any form of yoga in the previous 6 months and do not have a history of dementia. Patients will undergo a Mini-Mental State Exam (MMSE) with a score of at least 26 to rule out gross dementia. Additionally, they will be assessed using a CAIDE Risk Score (Cardiovascular Risk Factors, Aging, and Dementia) with a score of at least 6 points (18). Further, they will be excluded based on i) the presence of any neurological disorder; ii) significant arthritis; iii) recent acute infection or other inflammation; iv) persistent cognitive impairment due to psychoactive substance use; and v) individuals who have functional limitations that prevent them from walking or doing yoga and who have been advised against exercising by their physician or have undergone recent surgical interventions. Upon enrollment in the study, participants will be followed for 48 weeks (12 months) or until they withdraw from the study.

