### Study outcomes and assessments

#### Primary outcome

The primary objective of the study is to assess the efficacy of a yoga intervention vs. brisk walking at 48 weeks on the risk reduction of dementia. The primary endpoint is a difference in the CAIDE risk scores between the yoga and brisk walking groups after 48 weeks (12 months). As shown in CONSORT, assessments will be conducted at baseline, 24 and 48 weeks over 365 days with a 60-day flexibility window (Table 1). However, the primary time endpoint represents a longer-term outcome.

**Table 1 T1:** Schedule of enrolment, interventions, and assessments, according to SPIRIT 2013 guidelines

Time points	Screening Baseline	Intervention	Post-intervention	Endpoint
	week 0+2	24 weeks	24 + 1 week	48 + 1-week
Eligibility screening	x			
Informed consent	x			
Allocation	x			
** *Intervention* **		x		
Yoga/walking		x		
*Yoga*				
Phase I: supervised sessions		x		
Phase II: a synchronized yoga home practice		x	x	
*Control*		x	x	
Brisk walk: Weekly monitoring of daily steps				
*Assessments*				
Demographics and ApoE Genotype	x	x	x	x

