### Statistical analysis

Sample size: A sample size of 269 (n = 135; 135) was derived based on a moderate effect size assumption, using G power software’s formula for F-test, ANCOVA with fixed effect, main effect and main effect interaction model for 2 group comparisons. The calculated sample size also aligns with the estimate presented by Leon et al. 2009 (39). Further, assuming an attrition rate of 20%, the final sample size is n = 323 subjects randomized in a 1:1 ratio to yoga or brisk walking.Baseline characteristics will be presented using appropriate descriptive statistics. Before analysis, variable distributions will be examined to ensure that assumptions of normality are met using statistical software (SPSS, Statistical Package for the Social Sciences, Version 20.0) with the Shapiro-Wilk test. The equivalence of variance will be found using the F distribution test. Depending on the distribution of data, parametric or nonparametric tests will be performed within and between group comparisons for baseline data. The baseline characteristics of the study completers will also be compared with drop-outs. If the data will be skewed, non-parametric analysis through the Kruskal-Wallis test

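### Enrolment and the whole study carry the same dates (February 2023 to October 2024), although each participant needs 48 weeks to reach the primary endpoint; the two statements must be reconciled

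*Protocol article*

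**What the plan says.** Study Design dates the trial as a whole: "The study will be conducted between February 2023 and October 2024". Recruitment and screening uses the same two months for enrolment alone: "Participants will be enrolled using convenience sampling between February 2023 and October 2024". The same section then says that, once enrolled, "participants will be followed for 48 weeks (12 months) or until they withdraw from the study". The Primary outcome section places the primary endpoint, the between-group difference in CAIDE score, at 48 weeks (12 months).

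Study Design allows the 24- and 48-week assessments "with a 60-day window of flexibility", without saying whether visits may be early, late or both. The abstract reports "Recruitment began in February 2023 and is underway with patient enrollment". The Statistical analysis section sets the target: "assuming an attrition rate of 20%, the final sample size is n = 323".

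The article gives no later study end, no earlier close of enrolment and no separate follow-up period.

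**The concern.** A trial with a fixed follow-up of 48 weeks must run at least 48 weeks beyond its last enrolment. Here the two end dates coincide, so a participant enrolled in the final month would have almost no follow-up inside the stated study period.

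What is at stake depends on which date governs. If the study end governs while enrolment stays open, later participants never supply the week-48 CAIDE score, and the loss comes from the calendar rather than from dropout. The mixed model and the multiple-imputation sensitivity analysis can use earlier data from these people, but they cannot restore week-48 information that was not collected. If the enrolment window governs, the primary endpoint is complete about a year after the stated end of the study. The article reports recruitment as still open, so the date on which enrolment closes was a live decision.

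**Working it through.** **Inputs**

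- Study period and enrolment period: both February 2023 to October 2024 (Study Design; Recruitment and screening).
- Follow-up: 48 weeks = 48 × 7 = 336 days; the article also calls this 12 months (365 days). Table 1 heads the endpoint column 48 + 1 week (343 days).
- Visit window: 60 days, direction not stated (Study Design; Primary outcome).
- Sample size: 323; attrition allowance 20% (Statistical analysis).

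The article states no last-enrolment or last-visit date, so there is no figure of its own to reproduce.

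**Step 1: dates**

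Latest enrolment = 31 October 2024 − follow-up. Last visit = 31 October 2024 + follow-up.

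| Follow-up counted | Days | Latest enrolment if the study ends 31 Oct 2024 | Last visit if enrolment ends 31 Oct 2024 |
|---|---|---|---|
| 48 weeks, visit 60 days early | 276 | 29 Jan 2024 | 3 Aug 2025 |
| 48 weeks | 336 | 30 Nov 2023 | 2 Oct 2025 |
| 48 + 1 weeks | 343 | 23 Nov 2023 | 9 Oct 2025 |
| 12 months | 365 | 1 Nov 2023 | 31 Oct 2025 |
| 48 weeks, visit 60 days late | 396 | 1 Oct 2023 | 1 Dec 2025 |
| 12 months, visit 60 days late | 425 | 2 Sep 2023 | 30 Dec 2025 |

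These take the last day of October 2024 as the end. If the study ended on 1 October 2024, the 48-week cut-off would move from 30 November to 31 October 2023. Even the most generous row leaves February to October 2024, nine months of the stated enrolment window, too late.

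**Step 2: size, under the truncation reading only**

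Two assumptions are needed that the article does not supply: uniform accrual, and a start day within February 2023. Taking 15 February 2023 (the registration date), the window to 31 October 2024 is 624 days.

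Share with a week-48 visit by the stated end = (624 − follow-up days) / 624.

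- Day 276 (window used early): 348/624 = 55.8%, 180 of 323.
- Day 336: 288/624 = 46.2%, 149 of 323.
- Day 365: 259/624 = 41.5%, 134 of 323.
- Day 396 (every visit 60 days late): 228/624 = 36.5%, 118 of 323.

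Starting from 1 February 2023 (638 days) changes little: 362/638 = 56.7%, 302/638 = 47.3% and 242/638 = 37.9% for days 276, 336 and 396. Counting 12 months with every visit 60 days late is the extreme: 199/624 = 31.9%.

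**Step 3: comparison with the attrition allowance**

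The plan allows for 20% loss. For 48 weeks with the window, the calendar shortfall in Step 2 is 100 − 55.8 = 44.2% to 100 − 36.5 = 63.5%, before any dropout.

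**Step 4: the other reading**

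If enrolment runs to October 2024 and everyone is followed for 48 weeks, no endpoint is lost. The study end then moves from October 2024 to October 2025, or up to December 2025 with a late window.

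**The case against.** The strongest reply is that this is a misdescribed date range and not a plan to truncate follow-up. The follow-up sentence comes in the same paragraph as the enrolment dates and names withdrawal as the only early end. Nothing in the article sets a calendar cut-off for visits or analysis, and no interim analysis is planned. That argument stands: a wording error is at least as likely as truncation. It does not remove the point, because the article does not show which date is wrong and the two readings differ by about a year. Nor does condensation into a journal article explain it: two stated dates conflict, which is different from a detail left out.

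Two stronger readings are tempting and are not supported. A reader might infer that nobody enrolled after November 2023 can have a valid week-48 visit within the study period. The 60-day window has no stated direction, so an in-window visit is conceivable for enrolment up to about 29 January 2024.

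A reader might also infer that the trial would be underpowered. Taking 149 × 0.8 = 119 participants with week-48 data gives 77% power at a standardised difference of 0.5. Using the window early gives 180 × 0.8 = 144 and 85%. Those figures need full truncation, uniform accrual, a numerical value for what the article only calls a moderate effect, and no contribution from 24-week data in the mixed model. Faster early accrual would shrink the loss. They show sensitivity to the assumptions and should not be read as a property of the plan.

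**Conclusion.** The stated dates are incompatible with 48 weeks of follow-up, and this follows from the calendar alone. It matters more than a typing slip would, because keeping both dates literally would leave a large share of participants without the primary endpoint.

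The size is conditional. If follow-up stopped at the end of October 2024, roughly 37% to 56% of the 323 would have a week-48 visit; this assumes uniform accrual from mid-February 2023 and spans the 60-day window used late or early. If the enrolment dates are right, the loss is nil and only the stated study period is wrong. The article does not let a reader choose between the two, and it does not establish that any endpoint data have been or will be lost.

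**What to change.** Reconcile Study Design with Recruitment and screening by giving separate dates for:

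- first and last enrolment;
- the last 48-week visit, computed as last enrolment + 48 weeks + window, with the direction of the 60-day window stated.

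Then either close enrolment early enough for the stated study end or move the study end to match the enrolment window. In both cases every randomised participant should be able to reach the 48-week assessment before the primary analysis.

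The cost is a date correction and, if the study end moves, reporting about a year later. The endpoint, target sample size and analysis model are unchanged.

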### Study outcomes and assessments

#### Primary outcome

The primary objective of the study is to assess the efficacy of a yoga intervention vs. brisk walking at 48 weeks on the risk reduction of dementia. The primary endpoint is a difference in the CAIDE risk scores between the yoga and brisk walking groups after 48 weeks (12 months). As shown in CONSORT, assessments will be conducted at baseline, 24 and 48 weeks over 365 days with a 60-day flexibility window (Table 1). However, the primary time endpoint represents a longer-term outcome.

**Table 1 T1:** Schedule of enrolment, interventions, and assessments, according to SPIRIT 2013 guidelines

Time points	Screening Baseline	Intervention	Post-intervention	Endpoint
	week 0+2	24 weeks	24 + 1 week	48 + 1-week
Eligibility screening	x			
Informed consent	x			
Allocation	x			
** *Intervention* **		x		
Yoga/walking		x		
*Yoga*				
Phase I: supervised sessions		x		
Phase II: a synchronized yoga home practice		x	x	
*Control*		x	x	
Brisk walk: Weekly monitoring of daily steps				
*Assessments*				
Demographics and ApoE Genotype	x	x	x	x
** *Primary Outcome* **				
CAIDE dementia risk score	x	x	x	x

#### Secondary Outcomes

Secondary outcomes will include individual scores of CAIDE components and assessment scores of cognitive tests for memory, attention, language, verbal fluency, and executive ability, measured by neuropsychological tests or other objective measurements. The secondary clinical outcome of this study focuses on the 48-week change in the composite score of a comprehensive neuropsychology battery.

### Assessments

At the baseline and 48-week visits, the CAIDE score will be calculated using data on age, gender, self-reported years of formal education, systolic blood pressure, BMI, total cholesterol, physical activity, and ApoE status. Each component of the CAIDE score will undergo assessment, and a predetermined set of points will be allocated to each category of risk factors (17). The CAIDE score for each participant will be computed by summing up the points assigned to each risk factor category (18). Participants self-reported demographic details and physical activity levels, while healthcare professionals measured objective factors like systolic blood pressure, BMI, and blood cholesterol levels. The physical activity index was calculated based on activity duration and intensity. Genetic testing for ApoE ε4 carrier status was conducted during a specific exam. The CAIDE score, ranging from 0 to 18, will be used in a male-only cohort, with observed scores from 1 to 15 (18, 19).

At the outset, supplementary information encompassing demographic data and contemporary risk factors such as hypertension, diabetes, head injury, smoking, alcohol consumption, dyslipidemia, etc. will be documented for the participants.

This battery includes well-established tests to assess the global cognitive ability index as well as various domains of cognition such as memory, attention, language, verbal fluency, and executive ability, which will be measured by neuropsychological tests such as the Trail Making Test, Digit Span Test, N Back, Color Trail, Animal Fluency Test, COWA, and Digit Symbol Substitution.

In addition to the neuropsychology battery assessment, participants will also be asked to complete questionnaires to assess their quality of sleep using the Pittsburgh Sleep Quality Index (PSQI) and their overall quality of life using the World Health Organization Quality of Life (WHOQOL-BREF) questionnaire. These validated questionnaires provide valuable insights into participants’ subjective experiences of sleep quality and their overall well-being across physical, psychological, social, and environmental domains.

Furthermore, genotyping will be performed using DNA amplification through real-time PCR. This genetic analysis aims to explore potential associations between specific genetic variations and cognitive outcomes, providing insights into the role of genetics in cognitive function and dementia risk (22).

### Executive Function

#### Trail-making test

Trail-making test: A neuropsychological test of visual attention and task switching is called the Trail Making Test (23). There are two parts to it; part A seems to primarily depend on the effectiveness of visual scanning and psychomotor speed. In which the subject is asked to accurately connect a sequence of 25 dots as quickly as they can. Part B has circles with both numbers (1–13) and letters (A–L); the subject is instructed to connect the circles in an ascending pattern by alternating between the numbers and letters (i.e., 1-A-2-B-3-C, etc.) (23). Specifically, mental flexibility and a higher demand for working memory are required for executive control in TMT B. It is also capable of accurately identifying many cognitive disorders, including dementia and Alzheimer’s disease (23).

